### Plans to give access to the full protocol, participant-level data, and statistical code {31c}

Not applicable as no public access will be given.

## Oversight and monitoring {5d, 21a, 23}

The study will be monitored by the Malaysian Medical Research and Ethics Committee (MREC) and the IMU Joint Committee on Research and Ethics committee (IMUJC). The investigators will submit yearly and 6-monthly reports to MREC and IMUJC, respectively, on study progress and compliance to good clinical practice guidelines.

### Adverse event reporting and harms {22}

Contact information of the study investigators are enclosed in the study information sheet provided to the patients upon enrolment for reporting of potential adverse events (AEs) anytime. Potential adverse events may include any unfavourable sign and symptom, or increase in the severity of pre-existing disease, except anticipated occurrence of postoperative complications. Serious adverse events (SAEs) are defined as any untoward occurrence that results in death, is life-threatening, requires inpatient hospitalisation or prolongation of existing hospitalisation, results in persistent or significant disability/incapacity, or is a congenital anomaly/birth defect. All adverse events occurring during the study will be reported and documented on the AE form in patient’s folder whether or not they are considered to be non-serious, serious, and/ or related to treatment. The following information will be required in each case: patient and date, description of event, duration, frequency, intensity, seriousness, action taken, outcome and sequel and relationship to the product. The investigators will determine the potential causality between the study product and reported adverse events on the basis of the following criteria:
Unrelated: the AE is obviously explained by patient’s disease, in accordance with effect or adverse effect of concomitant medication or occurred prior to the administration of study product.Unlikely relation: there is reasonable temporal relationship with intake of study product but there is another plausible explanation for the occurrence of the AE.Probable relation: there is reasonable temporal relationship with intake of study product and there is plausible reason that points the AE to a causal relationship with the study product.Certain relation: there is reasonable temporal relationship with intake of study product, there is no other explanation of the AE, and the AE subsides on withdrawal of study product and recurrences on re-challenge the study product.

Patients who experience SAEs will be immediately withdrawn from the trial and these events will be reported to the principal investigator immediately. The principal investigator will then notify the Malaysian Medical Research and Ethics Committee (MREC) and International Medical University Joint Committee on Research and Ethics (IMUJC) immediately via phone followed by email of the AE form within 48 h. In case of serious adverse events persisting beyond trial termination, follow-up visit will be provided.

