#### Criteria for discontinuing or modifying allocated interventions {11b}

Patients will be withdrawn from the study if they wish to withdraw or experience serious adverse events (SAEs) for any reason.

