### Outcomes of the study {12}

The schedule of enrolment, interventions, and assessments for the study is shown in Table 1. The primary outcomes are body weight, body mass index (BMI), serum albumin, and pre-albumin level. The secondary outcomes include energy and protein intake, muscle and fat mass, handgrip strength, haemoglobin, serum transferrin, high sensitivity C-reactive protein (hs-CRP), interleukin-6 (IL-6), salivary cortisol, sleep quality, length of hospital stay, and postoperative complication rate within 30 and 90 days after surgery. The changes for these parameters will be assessed at a day prior to discharge (V3), 30 days after surgery (V4), and 90 days after surgery (V5) compared to baseline as shown in Table 2.

**Table 2 Tab2:** Outcome parameters’ description

Domain	Specific measurements	Metric and time points for assessment	Method of aggregation
Primary outcomes			
Nutrition status	Body weight, kg	Change from baseline (V1) at1 day prior to discharge (V3); change from 1 day prior to discharge (V3) at 30 days after surgery (V4); change from 1 day prior to discharge (V3) at 90 days after surgery (V5)	Mean
	BMI, kg/m^2^		
	Serum albumin, g/L		
	Serum prealbumin, mg/L		
Secondary outcomes			
Nutrition status	Handgrip strength, kgF	Change from baseline (V1) at 1 day prior to discharge (V3); change from 1 day prior to discharge (V3) at 30 days after surgery (V4); change from 1 day prior to discharge (V3) at 90 days after surgery (V5)	Mean
	Muscle mass, kg		
	Fat mass, kg		
	Serum transferrin, g/L		
	Haemoglobin, g/dL		
Inflammation	High-sensitivity C-reactive Protein (hs-CRP), mg/L		Mean
	Interleukin-6 (IL-6), pg/ml		
	Salivary cortisol, μg/dL		
Dietary intake	Energy intake, kcal/d		Mean
	Protein intake, g/d		
Sleep quality	Pittsburgh Sleep Quality Index (PSQI) score		Median
Postoperative complications	Postoperative complications	Frequency of postoperative complications at discharge (V3), at 30 days after surgery (V4), and 90 days after surgery (V5)	Median
	Length of hospital stay	Number of days of hospitalisation from admission (V1) to 1 day before discharge (V3)	Median

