#### Postoperative complications

The postoperative complications are defined as any deviation from the normal postoperative course and divided into minor and major complications. Minor complications include minor risk events, such as wound infection, urinary tract infection, or postoperative ileus [43]. Major complications include potentially life-threatening complications and those with a need of surgical, endoscopic, or radiological intervention, such as an anastomotic leak, abdominal abscess, and pneumonia [43]. Any readmission to the hospital for 30 and 90 days after surgery is to be recorded including the length of hospital stay and reason of readmission.

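### A serious adverse event ends study participation, not only the supplement, so a readmission can stop the 90-day follow-up meant to count later events

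*Protocol article*

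**What the plan says.** All references are to the protocol article.

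- **Withdrawal rule, section {22}:** "Patients who experience SAEs will be immediately withdrawn from the trial".
- **Withdrawal rule, section {11b}:** "Patients will be withdrawn from the study if they wish to withdraw or experience serious adverse events (SAEs) for any reason".
- **SAE definition, section {22}:** besides death, disability and congenital anomaly, it covers an event that "is life-threatening, requires inpatient hospitalisation or prolongation of existing hospitalisation".
- **Exception, section {22}:** the description of adverse events ends with "except anticipated occurrence of postoperative complications". The term anticipated is not defined, and the exception is not repeated in the SAE definition or in either withdrawal rule.
- **Outcomes, section {12}:** the secondary outcomes include "length of hospital stay, and postoperative complication rate within 30 and 90 days after surgery". Table 2 defines the later continuous outcomes as change from the day before discharge (V3) to day 30 (V4) and day 90 (V5).
- **Postoperative complications, under {18a}:** "Any readmission to the hospital for 30 and 90 days after surgery is to be recorded", together with its reason and length. Major complications include potentially life-threatening ones.
- **Analysis, sections {18b}, {20a} and {20c}:** the primary analysis is per protocol and needs both a completed intervention and attendance at every visit. The secondary ITT analysis keeps all randomised patients and fills gaps by last observation carried forward (LOCF).

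The only later contact described after an SAE is a follow-up visit when the event persists beyond the end of the trial. That is safety follow-up, not outcome collection.

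**The concern.** Two decisions are merged into one rule. Whether a patient goes on taking the supplement is a clinical matter. Whether the patient's outcomes are still observed is a matter of design, and nothing in the first decision requires the second to follow it.

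The merger matters here because the SAE criteria overlap with what the trial measures. A readmission is an inpatient hospitalisation, so an event that has to be recorded can also be the event that closes the record. Some major complications meet the life-threatening or prolonged-stay criteria in the same way. Follow-up then ends for a reason related to the outcome. If supplementation alters complication or readmission rates, as the Discussion suggests on the basis of earlier studies, the loss may differ between arms, and recruiting more patients would not remove the resulting bias.

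**Working it through.** **1. The sections side by side.** Take a Group SS or DS patient who is discharged and then readmitted before day 30 for a reason that is not an anticipated postoperative complication.

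- Sections {6b} and the Abstract: the allocated supplement ended at discharge, so there is no supplement left to stop.
- Section {22}: the readmission meets the hospitalisation criterion and is an SAE.
- Sections {11b} and {22}: the patient is withdrawn from the study.
- Postoperative complications and Table 2: this readmission, any later one, complications to day 90, and the V4 and V5 values are all still required.

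For this patient the withdrawal rule changes only what data are collected.

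**2. Per-protocol set (primary analysis).** A patient withdrawn before V5 has not attended all visits and is excluded.

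**3. ITT with LOCF (secondary analysis).** Let Y1 to Y5 be the values at V1 to V5, with a star for an imputed value.

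- Withdrawn between V3 and V4: Y4* = Y5* = Y3. The changes from V3 are Y4* − Y3 = 0 and Y5* − Y3 = 0, whatever happened to weight, BMI, albumin or prealbumin.
- Withdrawn between V4 and V5: Y5* = Y4, so the day-90 change repeats the day-30 change.
- Withdrawn after surgery but before V3: Y3* = Y2, or Y1 if V2 is missing. A preoperative value stands in for the postoperative one.

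The direction of the resulting error is not fixed. A preoperative value carried forward hides a postoperative fall. A low V3 value carried forward hides any recovery by day 30 or 90.

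**4. Size.** The article gives no SAE rate, so no estimate can be made. The table shows only what a given rate r would do, assuming that every such patient is withdrawn before V5, that no exception applies and that there is no other loss. Inputs from section {14}: 28 per group, 84 in total, difference 4 g/L, SD 6.5 g/L, alpha 5%, taken here as two-sided. Remaining per group = 28 × (1 − r). Withdrawn = 84 × r. Approximate power for one pairwise comparison = Φ(4 / (6.5 × √(2/n)) − 1.96).

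| Assumed r | Withdrawn of 84 | Left per group | Power |
|---|---|---|---|
| 0% | 0 | 28 | 63% |
| 5% | 4.2 | 26.6 | 61% |
| 10% | 8.4 | 25.2 | 59% |
| 20% | 16.8 | 22.4 | 54% |
| 30% | 25.2 | 19.6 | 49% |

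The plan has 28 − 23 = 5 patients per group in reserve, and 5/28 = 18%. Only an SAE rate of about that size would use up the reserve by itself.

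The planned 28 gives 63% rather than 80% for a separate reason. The stated inputs do not reproduce 23 per group for a between-group comparison: 2 × 6.5² × (1.96 + 0.84)² / 4² is about 41.4, so 42. That is not part of this point.

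**The case against.** **The exception may remove much of the overlap.** Section {22} excepts anticipated postoperative complications from adverse events and then treats SAEs as one kind of adverse event, so the exception can be read as carrying over. On that reading, wound infection, ileus, leak, abscess or pneumonia, and a readmission caused by one of them, might trigger no withdrawal. The reading is possible. Against it, the exception is not restated where it would matter, anticipated is undefined, and section {11b} covers SAEs for any reason. Even on the generous reading, other readmissions still end participation. What stands is that the number affected cannot be inferred from the text.

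**Some of the data survive.** The triggering event goes on the adverse event form and is reported, and length of the index stay comes from hospital records. This stands. What is at risk is what comes after. Readmission is also a recorded item under complications, not a separately listed outcome.

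**The per-protocol definition does part of the damage.** This stands too. A Group SS-E patient who stopped the supplement after an SAE would be excluded by section {20a} even if followed to day 90.

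**The heading of {11b} concerns discontinuing interventions, and a journal article is condensed.** The heading gives some support for reading withdrawal as withdrawal from the supplement, but the wording there is from the study, and {22} says from the trial. The point rests on a rule stated twice, not on a missing detail.

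**A stronger reading is tempting.** A reader might infer that the sickest patients vanish from every analysis, that albumin and weight will therefore look better at days 30 and 90, or that a sizeable known share of each arm is lost. The documents do not support this. ITT keeps these patients, the direction under LOCF can go either way, and no SAE rate is given.

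**Conclusion.** The concern holds in a limited form. As written, the rule ends follow-up after any SAE, and the SAE criteria overlap with the events that the trial is to record to day 90. The consequences that follow from the text are three:

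- events and visit values after the SAE have no stated route into the data;
- the patient leaves the primary per-protocol analysis;
- in ITT, carried-forward values replace the later measurements, with a change from V3 of zero for withdrawal between V3 and V4.

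The missingness is related to outcome and may differ by arm. Its size is unknown, and so is its direction in ITT. Both depend on the SAE rate, which the article does not give, and on whether the exception for anticipated complications reaches the withdrawal rule, which the article does not settle. The conclusion assumes that the rule is followed literally. If staff in practice go on collecting data after an SAE, the text needs to say so.

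**What to change.** Amend the protocol in three places.

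1. **Follow-up.** State that, after an SAE, outcome data are collected through V5, from hospital records at minimum, unless the patient withdraws consent for this. Keep this separate from any statement about the supplement. Whether the supplement stops after an SAE is a clinical decision left to the sponsor.
2. **Analysis.** State that such patients are analysed in their allocated arm using the observed values, so that LOCF is not applied where a measurement exists.
3. **Reconciliation.** Bring sections {11b} and {22} and the Postoperative complications text into agreement. Define anticipated, and say whether the exception applies to SAEs and to the withdrawal rule.

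The change restores observed data mainly for ITT, and for patients in the per-protocol set whose allocated supplement was already complete. It does not alter the per-protocol definition itself.

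The cost is small: a short amendment with ethics notification. The day-30 and day-90 visits are already scheduled at the surgical outpatient clinics, and hospital records are already a data source. The article reports the trial as still enrolling, and values not collected at those visits cannot be recovered later, so the amendment is best made promptly.

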#### Length of hospital stay

The length of hospital stay is calculated from the day of admission up to 1 day prior to being discharged from the hospital. The information is obtained from patients’ hospital records.

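### Any serious adverse event ends trial participation, not only the supplement, so outcomes after the event are not collected; whether anticipated complications count as serious events is left open

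*Protocol article*

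**What the plan says.** Two places in the protocol article set the rule. Section 11b, on discontinuing interventions, says "Patients will be withdrawn from the study if they wish to withdraw or experience serious adverse events (SAEs) for any reason". Section 22, on harms, repeats it: "Patients who experience SAEs will be immediately withdrawn from the trial". The only visit promised after such an event is a narrow one: "In case of serious adverse events persisting beyond trial termination, follow-up visit will be provided".

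Section 22 defines an SAE as "any untoward occurrence that results in death, is life-threatening, requires inpatient hospitalisation or prolongation of existing hospitalisation", with further criteria for disability and congenital anomaly. Just before this, the description of adverse events carries an exception: "except anticipated occurrence of postoperative complications". The SAE definition does not repeat it.

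The planned outcomes overlap with these events. Section 12 lists the "postoperative complication rate within 30 and 90 days after surgery" as a secondary outcome. The section on postoperative complications says "Major complications include potentially life-threatening complications and those with a need of surgical, endoscopic, or radiological intervention", and asks for readmissions to be recorded at 30 and 90 days with their reason and length of stay.

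Section 20a makes a per-protocol analysis primary. It is limited to patients who completed their allocated product and attended every visit. The intention-to-treat (ITT) analysis is secondary and fills gaps by last observation carried forward (LOCF).

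**The concern.** Stopping a product after a serious event is a safety decision. Ending outcome assessment is a different decision, and the article ties the two together for every SAE, related to the supplement or not. The patients lost are those with the worst course, so the missingness depends on outcome.

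The complication outcomes are the most exposed. If a serious complication counts as an SAE, the event that the trial wants to count ends the patient's observation for further events of the same kind. The Discussion cites studies in which supplementation lowered complication rates. If that were true here, withdrawals triggered by complications would differ between arms and distort the comparison.

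**Working it through.** The article gives no figure on this point to reproduce, so the check is mainly one of reading the sections against each other.

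**Step 1: scope of the rule.** Section 11b says study and section 22 says trial. Neither has a rule for stopping the product alone, and neither provides for visits V3 (day before discharge), V4 (day 30) or V5 (day 90) after withdrawal. Outcome visits lost per withdrawn patient:

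| SAE occurs | Visits lost |
|---|---|
| before V3 | V3, V4, V5 |
| between V3 and V4 | V4, V5 |
| between V4 and V5 | V5 |

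**Step 2: does anything else recover the data?** Section 18b keeps drop-outs' data in the ITT analysis, and the triggering event can itself be counted. But LOCF (sections 20a and 20c) repeats an earlier measurement; it cannot supply a later complication or readmission. The visit for SAEs that outlast the trial does not replace V3 to V5. In the per-protocol analysis, a patient who misses any visit is out.

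**Step 3: the two readings of section 22.**

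| | Exception does not reach SAEs | Exception reaches SAEs |
|---|---|---|
| Complication prolonging stay or causing readmission | is an SAE; patient withdrawn | not an SAE; patient stays |
| Later complications and readmissions | not collected | collected |
| Adverse event form, relatedness grade, 48-hour committee notice | required | not required |
| SAE that is not an anticipated complication | patient withdrawn | patient withdrawn |

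The last row is the same in both columns, so the rule costs follow-up whichever reading is meant.

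**Step 4: where withdrawal protects nobody.** Section 6b stops the product at discharge in groups SS and DS, which are 2 × 28 = 56 of the 84 planned patients. For an SAE after discharge in these groups there is no product left to stop. Withdrawal only loses data.

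**Step 5: illustration of size.** Let p be the share of randomised patients withdrawn under the rule. The article gives no SAE or complication rate, so p is assumed. Expected withdrawals are 84p in the trial and 28p per arm. The chance that the rule is used at least once is 1 − (1 − p)^84. Section 14 gives 28 recruited and 23 needed per arm, so the allowance is 28 − 23 = 5. With X ~ Binomial(28, p), P(X > 5) is the chance that these withdrawals alone exceed it in a given arm.

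| p (assumed) | 84p | 28p | At least one | P(X > 5) |
|---|---|---|---|---|
| 2% | 1.7 | 0.6 | 82% | under 0.01% |
| 5% | 4.2 | 1.4 | 98.7% | 0.2% |
| 10% | 8.4 | 2.8 | over 99.9% | 5.5% |

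Only at about 20% would the allowance be used up on average (28 × 0.20 = 5.6). The at-least-one column shows that the rule would probably be applied, not that it would bias a result.

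**The case against.** The strongest reply is that the exception does reach SAEs. A serious adverse event is ordinarily a kind of adverse event, and section 22 treats it so when it asks for all adverse events, serious or not, to be documented. A plan that records major complications and readmissions to day 90 hardly intends the first one to end participation. This is a reasonable reading, perhaps the more coherent one. A reader might infer that every serious complication certainly ends follow-up; the text does not establish that. What remains is that the article does not say which reading holds, and that any other SAE ends follow-up on both.

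A reader might also infer that, if the exception does reach SAEs, serious complications go unreported. The documents do not support this. Section 12 and the section on postoperative complications still record them as outcomes, with readmission reasons. Only the adverse event form, the relatedness grade and the committee notice are lost.

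Three further points stand in part:

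- Length of stay comes from hospital records, and the article does not say that record review stops on withdrawal, so its loss should not be assumed.
- Section 11b sits under a heading about interventions, which leaves some doubt about intent, although its wording and that of section 22 end participation.
- The per-protocol choice removes many of these patients anyway: someone too ill to finish the supplement is excluded whatever the withdrawal rule says.

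A fuller protocol may settle whether complications count as SAEs. The withdrawal rule, however, is stated outright in the article and is not a detail left for elsewhere.

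**Conclusion.** The point holds in this form: the withdrawal rule, followed as written, discards planned outcomes after any SAE, and the reach of the complication exception is unclear. The first part is explicit text and holds on either reading. The second is an ambiguity, and its consequence depends on the reading: lost complication follow-up, or no safety processing of serious complications.

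The size is unknown. The counts above rest wholly on assumed shares. At 2% to 10%, the sample-size allowance would rarely be exceeded by these withdrawals alone, so a claim that the rule leaves the trial short of patients is not supported. The issue is which patients are lost. Unequal loss between arms is a further condition, resting on an effect on complications that this trial has yet to show. The rule should be changed, since doing so is cheap, but the documents do not show that a primary result will be materially biased.

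**What to change.** Amend sections 11b and 22 so that an SAE stops the product where clinically needed, while V3 to V5 follow-up continues unless the patient withdraws consent. In section 22, state that a postoperative complication meeting a seriousness criterion is reported as an SAE and graded for relatedness.

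This restores observed data to the ITT analysis and to the 30- and 90-day complication outcomes. It also keeps in the per-protocol set patients who had finished their product or continue it, such as SS and DS patients with an event after discharge. It does not return to that set patients whose product is stopped early; that follows from the definition of the set.

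The cost is wording in two sections, a few more adverse event forms, and visits that are already in the schedule.
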